#### 2.2.2. Phase 2: Efficacy Test

Participants assigned to the intervention group downloaded an application called HAPPY ME. Consenting parents and children in the intervention group participated in a workshop before baseline at each school. This workshop was led by the research team to explain the study protocol, as well as the use of the HAPPY ME application and the wearable device. During the 12-week trial, students use a wearable device called the Walkie + D Coffee. Physical activity data collected by the wearable device are transmitted directly to the HAPPY ME application. Use of the application helps children self-monitor their behavior in terms of physical activity and dietary habits. Students participated in two group education sessions at weeks 4 and 8, both of which focused on a healthy diet and physical activity. Physical Activity Promotion System (PAPS) testing and lifestyle questionnaires were conducted at the baseline and are planned for the final week of the trial.

#### 2.2.3. Phase 3: Long-Term Effect Test

Following the 12-week efficacy test, the intervention group will voluntarily continue using the application and the wearable device during a six-month follow-up period to test the long-term effects of the intervention in terms of preventing obesity. After the follow-up period, the children’s application access log and performance data will be collected by the research team. At month 6, both the intervention group and the control group will complete lifestyle questionnaires and assessment via PAPS measurement.

### 2.3. Data Collection

Primary outcome measures are behavioral changes, including healthy eating, increased physical activity according to the application and questionnaire responses, and fitness measurements from the PAPS. Secondary outcome measures are changes in anthropometric parameters (body weight, height, BMI z-scores, obesity prevalence, and waist circumference) based on PAPS, BMI percentile, and psychological variables, such as self-body perception and sleep hours, reported in the questionnaires. Information from PAPS was measured at the time of enrollment, as well as at three months and at nine months following the trial.

### 2.4. Statistical Analysis

Data is analyzed using statistical software SPSS (version 21.0, IBM Corp., Armonk, NY, USA). Body mass index (BMI) is expressed in percentile according to Korean growth charts [33]. Comparisons of continuous variables between groups within sexes are performed using unpaired *t*-tests or Wilcoxon or Mann-Whitney tests as appropriate, after testing variables for normality of distributions and equality of variances. Comparisons of continuous variables after the trial within groups are performed using paired *t*-tests, Mann-Whitney U tests, or Wilcoxon signed ranks test as appropriate. Chi-square tests or Fisher’s exact probability tests are used to test differences between groups for categorical variables. Comparisons between groups of combined sexes are performed using linear (continuous outcomes) or logistic (categorical outcomes) regressions adjusted for sex, baseline BMI z-score, duration of application usage, and school.

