## Abstract

*Background*: Childhood obesity is a critical health issue, both currently and for the foreseeable future. To prevent obesity, behavior changes are essential. Smartphones can be a good tool, as the number of child smartphone users is rapidly increasing. We have developed a mobile platform system named “HAPPY ME,” which is a smartphone application coupled with a wearable device, designed to improve healthy behaviors to prevent childhood obesity. This study aimed to evaluate the effectiveness of obesity prevention among children 10–12 years of age using HAPPY ME. *Methods*: A total of 1000 participants, all fifth and sixth graders from four schools, were assigned to either control or intervention groups by school. Students in the intervention group used HAPPY ME. The study comprises a safety test, a 12-week efficacy test, and a six-month follow-up test to determine the long-term effects of preventive intervention via the integrated service platform. The integrated service platform aims to facilitate child-parent-school participation, involving the child-parent mobile application, a child-teacher mobile web, and a school website. Primary outcome measures are behavioral changes, including healthy eating, increased physical activity, and fitness. Secondary outcome measures are changes in anthropometric parameters (body weight, height, body mass index z-score, and waist circumference), body mass index (BMI) percentiles (obesity rate), and psychological perceptions among participants. *Conclusions*: The results of this study will offer evidence of the effectiveness of a mobile platform service with a multi-component intervention program based on a comprehensive approach.

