
## 2. Methods

### 2.1. Study Participants

Participating schools were recruited by a sanctioned announcement involving official letters from the Metropolitan and Provincial Offices of Education in Gyeonggi Province. Since the recruitment publicity included information regarding the use of mHealth to tackle childhood obesity, the study could not be masked and all applicant schools wished to be designated as intervention schools. We took pragmatic approach to intervention and control group allocation due to the fact schools were unwilling to be randomized. According to our pilot study conducted the previous year, less than 40% of students in fourth grade have smartphones, which can lead to a serious selection bias. The pilot study showed that the number of students who own smartphones increases as students advance through grades at school. Therefore, we determined that fifth and sixth graders were eligible to participate in our research by following a nine-month-long study using smartphones and wearable devices for the prevention of childhood obesity. The sample size was determined based on the government funding, the feasibility of the study, the number of measurements per participant, the number of students we could recruit, and the potential dropout rate considering the age of participants rather than the effect sizes of the intervention. We chose 250 students from each school as an appropriate number, for a total of 1000 students across four participating schools. To categorize children’s weight status, we used the standard growth chart for infants and children by the Korea Centers for Disease Control and Prevention [33]. Written consent was collected from all participating children and their parents. Inclusion criteria were fifth-sixth graders (10–12 years old), no previous diagnosis of systemic or metabolic diseases, and Android smartphone users with parental consent, students who did not refuse to participate (see Figure 1). Finally, 288 students were assigned to a control group, and 558 students were allocated in the intervention group. Any physical restrictions in participants were assessed during meetings with teachers and in loading the program to the smartphone applications of participants.

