#### 2.1.1. Control Group

Students in the control group underwent the same measurements as students in the intervention group, including Physical Activity Promotion System (PAPS) measurements and lifestyle questionnaires administered at the baseline, at week 12, and at month 6. Comprehensive assessments of dietary habits, physical activities, and psychological variables are planned for each assessment period using questionnaires. The control group received the same two group education sessions. Data for these 250 students from one elementary school were collected.

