### 2.2. Study Design

The current study is a school-based nonrandomized controlled trial funded by a national grant to prevent childhood obesity in Korea, which has been undertaken utilizing a safety test, a 12-week efficacy test, and a planned subsequent six-month follow-up test for long-term effects. During the study period of 37 weeks, participating students are expected to use their smartphones along with a wearable device, while parents and teachers will receive feedback messages about the performance of participants via smartphones and teacher websites. Data is collected on the part of the research team by monitoring the HAPPY ME platform and spot feedback from teachers and children. For the feedback session with children, our research team will be assigned to each school for three months. A group meeting with parents and teachers for feedback is planned to occur during the three-month efficacy trial. To evaluate the students’ physical performance, data collected by the Physical Activity Promotion System (PAPS) from each school will be monitored. Reporting PAPS data is mandatory in the Korean school system. The PAPS consists of tests to assess cardiac endurance, muscle strength, power, flexibility, and body composition. The PAPS was developed by the Korean government according to public interest in health concerning the growing number of obese and/or weak children. Every elementary school performs PAPS testing once or twice a year to measure student health and, based on results, offers individual exercise prescriptions to every participant. For the schools participating in the application efficacy trial herein, participating students will perform PAPS testing before and after the trial under the guidance of experienced examiners to test the participants’ overall physical fitness, including obesity evaluation, by measuring percent body fat using bioelectrical impedance analysis (BIA). A lifestyle questionnaire which was designed and internally validated was conducted at the beginning of the trial. The questionnaire will also be conducted at week 12 and at the end of the trial. The questionnaire consists of behavioral factors regarding sleep, stress, dietary habits, and activity habits, as well as the amount of screen time by participating children and psychological factors, such as body image. Every participant is required to attend two group education sessions at their respective schools featuring information on a healthy diet and food additives, as well as easy-to-learn physical activities from professionals at week 0 and at week 8 during the 12-week efficacy test period (see Table 1).

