
## 4. Conclusions

The results of this study will offer evidence of the effectiveness of a mobile platform service with a multi-component intervention program based on a comprehensive approach.

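### Section 2.4 tests children as independent although four whole schools (one control) were allocated, so p-values are too small by an ICC-dependent amount, and the school-adjusted regression cannot estimate the group effect

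*Protocol article*

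**What the plan says.** The design is stated clearly. Section 2.2 says "The current study is a school-based nonrandomized controlled trial", and the Abstract says that participants "were assigned to either control or intervention groups by school". Section 2.1 plans 250 students per school, "for a total of 1000 students across four participating schools", a number set by funding and feasibility "rather than the effect sizes of the intervention". It then reports 288 control and 558 intervention children. Section 2.1.2 refers to three intervention schools. Section 2.1.1 says of the control arm: "Data for these 250 students from one elementary school were collected".

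Section 2.4 lists the between-group methods:
- Continuous outcomes: "Comparisons of continuous variables between groups within sexes are performed using unpaired" t-tests, or rank tests where appropriate.
- Categorical outcomes: chi-square or Fisher tests.
- Both sexes combined: linear or logistic regression adjusted for sex, baseline BMI z-score, duration of application use, and school.

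No random school effect, generalised estimating equation, cluster-robust error or school-level analysis is named. The limitations in section 3 cover the lack of randomization and of blinding, but not clustering or the single control school. Section 4 concludes: "The results of this study will offer evidence of the effectiveness of a mobile platform service".

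**The concern.** When whole schools are allocated, children in one school share whatever makes that school differ from the others, and part of the intervention is itself delivered through teachers and classes. The uncertainty of the group difference then has two parts: variation between schools, averaged over one control and three intervention schools, and variation between children. The listed t-tests, rank tests and chi-square or Fisher tests contain only the second part. Recruiting more children shrinks the second part and leaves the first untouched.

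The regression has a different and more basic fault. Every child's group follows from the child's school, so a model with both terms has no information left for group.

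At stake is the main comparison on the behavioural and fitness outcomes of section 2.3. A difference that reflects only which school served as control could be reported as a significant effect of the platform.

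**Working it through.** **Planned size.** 4 × 250 = 1000, as stated. Allocated: 288 + 558 = 846. The article gives no alpha, power, effect size, SD or ICC, so there is no power figure to reproduce.

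**Inputs.** From section 2.1: 288 control and 558 intervention children. From sections 2.1.1 and 2.1.2: one control and three intervention schools. Assumed: two-sided alpha 0.05; equal intervention schools (558/3 = 186 each); half of each arm in each sex (144 v 279); school ICC from 0.001 to 0.05.

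**Formulas**, in units of the outcome variance, with n_c control and n_i intervention children:
- Variance that the planned tests assume: V0 = 1/n_c + 1/n_i
- Variance with school variation: V = ICC × (1 + 1/3) + (1 − ICC) × V0
- Actual type I error: 2 × [1 − Φ(1.96 / √(V/V0))]

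**Numbers.** Pooled: V0 = 1/288 + 1/558 = 0.00526 (SE 0.073 SD). Within one sex: V0 = 1/144 + 1/279 = 0.01053 (SE 0.103 SD). As an example, within one sex at ICC 0.01: V = 0.01333 + 0.99 × 0.01053 = 0.02376; V/V0 = 2.26; SE ratio 1.50; type I error 2 × [1 − Φ(1.96/1.50)] = 0.19.

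| Assumed school ICC | SE ratio, one sex | Type I error, one sex | SE ratio, pooled | Type I error, pooled |
|---|---|---|---|---|
| 0.001 | 1.06 | 6.5% | 1.12 | 8% |
| 0.005 | 1.28 | 12.5% | 1.50 | 19% |
| 0.01 | 1.50 | 19% | 1.88 | 30% |
| 0.02 | 1.87 | 30% | 2.46 | 43% |
| 0.05 | 2.70 | 47% | 3.69 | 60% |

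Simulated pooled t-tests (4000 runs each) gave 0.30, 0.43 and 0.59 at ICC 0.01, 0.02 and 0.05, in agreement with the formula.

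**Regression.** With school entered as a categorical covariate, the intercept, group and three school dummies make 5 columns of rank 4, so group is fully aliased with school. If the software drops one dummy, the group coefficient becomes the control school against one arbitrary intervention school. Its simulated type I error is still 0.30, 0.40 and 0.59 at ICC 0.01, 0.02 and 0.05.

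**What the design can support.** A comparison of school means, with the between-school variance borrowed from the three intervention schools, has 2 degrees of freedom and a critical t of 4.30. Its simulated type I error is 0.044 to 0.048. With 80% power it detects about 0.77, 1.01 and 1.51 SD at ICC 0.01, 0.02 and 0.05. Treating 846 children as independent suggests 0.20 SD.

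**ICC at which significance is lost.** Solving d = 1.96 × √V for a pooled difference d in SD units gives ICC = (d²/1.96² − V0) / (4/3 − V0). For d = 0.20: (0.01041 − 0.00526) / (1.33333 − 0.00526) = 0.0039. A pooled difference of 0.20 SD therefore stops being significant once the school ICC passes about 0.004.

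**The case against.** Four points can be made for the plan.

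- **The size rests on an ICC that the article does not give.** This stands. At ICC 0.001 the inflation is slight (6.5% within sex, 8% pooled). The outcomes are changes, so stable differences between schools partly cancel, and the relevant ICC is that of the change. A reader might infer that the p-values are far too small whatever the ICC; the document does not support that.
- **The continuous tests run within sex.** This also stands. A reader might apply the pooled 19% to 60% (ICC 0.005 to 0.05) to the t-tests, but those figures fit only tests on all 288 v 558 children, perhaps the chi-square and Fisher tests, whose sex stratification is left open.
- **The regression adjusts for school.** This does not help. It would also be inaccurate to say only that this model's standard errors are too small: its first fault is that the group effect is not estimable.
- **The limitations already admit non-randomization and possible bias and promise control of confounders, and no confirmatory test is declared.** Partly fair: section 4 is a general, forward-looking sentence and not a formal claim. But confounder control does not supply the missing between-school variance, and neither clustering nor the single control school is mentioned.

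The absence of a separate analysis plan is no answer, because section 2.4 states the tests.

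**Conclusion.** The point holds, with its size conditional on the ICC. No listed t-test, rank test, chi-square or Fisher test reflects the allocation of four schools. The resulting type I error is about 6.5% to 47% within one sex and 8% to 60% for any pooled test, over assumed school ICCs of 0.001 to 0.05; within one sex it is more than double the nominal 5% from ICC 0.005 upward. These figures rest on equal intervention schools, an even split by sex and a two-sided 5% level. The regression fault needs no ICC: with school as a categorical covariate, the group effect cannot be estimated.

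No model removes the underlying limit. With one control school, the platform's effect cannot be separated from that school's own effect, and between-school variance in the control arm cannot be estimated. The control count differs between sections 2.1 (288) and 2.1.1 (250). Using 250 moves the pooled type I error at ICC 0.01 only from 30% to 28%, so the conclusion is unchanged.

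**What to change.** In section 2.4:
- Remove school as a fixed covariate from the group comparison.
- Report the group difference with its standard error recomputed over a stated range of school ICC (for example 0.001 to 0.05), and the ICC at which significance is lost. Alternatively, report a school-level comparison and state that it has at most 2 degrees of freedom.
- Show each intervention school against the control school.
- Treat between-group p-values as exploratory.

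A class random intercept alone is not a remedy, because it omits school variance. In a simulated class-level comparison (assumed 10 equal classes per school, no extra class variance), type I error stayed at about 13%, 21%, 33% and 47% at school ICC 0.005, 0.01, 0.02 and 0.05. Section 2.1.2 also describes the teacher website for the intervention schools only, so it cannot be assumed to identify classes in the control school.

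In section 3, name clustering and the single control school as limitations. There, in section 4 and in the Abstract, reword the conclusion to a difference observed between these four schools. Reconcile the control count in sections 2.1 and 2.1.1.

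The cost is some extra analysis, wider intervals and a softer conclusion. No new schools or data are needed.

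### Section 2.4 names only one-visit and two-visit methods for a three-visit design, which leaves the month-6 comparison open to bias from differential dropout and specifies no contrast between the week-12 and month-6 effects

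*Protocol article*

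**What the plan says.** **Visits.** Section 2.1.1 of the protocol article has "lifestyle questionnaires administered at the baseline, at week 12, and at month 6" for the control group, with the same measurements as the intervention group. Table 1 shows questionnaires and PAPS at those three points in both groups.

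**Long-term objective.** Section 2.2.3 has the intervention group continue voluntarily with the app and device "during a six-month follow-up period to test the long-term effects of the intervention in terms of preventing obesity". It adds: "At month 6, both the intervention group and the control group will complete lifestyle questionnaires and assessment via PAPS measurement". Section 2.3 times PAPS at enrolment, "as well as at three months and at nine months following the trial". I read this as counted from enrolment, so that nine months is the visit called month 6 elsewhere (12 weeks plus six months).

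**Methods (section 2.4).**
- Between groups, within sex: "Comparisons of continuous variables between groups within sexes are performed using unpaired *t*-tests or Wilcoxon or Mann-Whitney tests as appropriate".
- Within groups: "Comparisons of continuous variables after the trial within groups are performed using paired *t*-tests, Mann-Whitney U tests, or Wilcoxon signed ranks test".
- Categorical outcomes: chi-square or Fisher tests.
- Between groups, sexes combined: "Comparisons between groups of combined sexes are performed using linear (continuous outcomes) or logistic (categorical outcomes) regressions", with sex, baseline BMI z-score, length of app use and school as covariates.

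The section does not say which visit or pair of visits each method serves. It names no visit or group-by-visit term.

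**Dropout.** Section 2.1 lists "the potential dropout rate considering the age of participants" among the considerations behind the sample size and gives no rate.

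**The concern.** Section 2.4 commits to named tests and named covariates, so the methods are a stated choice and not something left to another document. The choice does not fit three visits, for three reasons.

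1. A child seen at week 12 but not at month 6 adds nothing to a month-6 test on observed data, although the week-12 value says how that child was doing. If lower-scoring children leave more often in one group than in the other, the children left at month 6 are no longer comparable, and an apparent long-term effect can arise where none remains.
2. The combined-sex regression adjusts for baseline BMI z-score. For the primary outcomes (eating behaviour, activity, fitness) that is not the outcome's own baseline, so a safeguard that would remove part of this bias is absent.
3. Whether a week-12 effect lasts is a question about the difference between two group effects. Setting a week-12 p-value beside a month-6 p-value, possibly from different sets of children, does not test it. A within-group paired test does not either, because growing children change in both groups.

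**Working it through.** **Figures from the article.** Planned total: 4 × 250 = 1000, as stated. Allocated: 288 control and 558 intervention, 846 in all. No dropout rate, SD or effect size is given, so the size of any bias cannot be derived from the article. What follows illustrates it under assumptions.

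**Assumptions, first simulation** (2000 replicates per case): 288 v 558 children; outcome SD 1; correlation 0.6 between every pair of visits; week-12 effect 0.2 SD; true month-6 effect 0. Controls drop out at random at 10%. In the intervention group dropout is likelier with a lower week-12 score (log-odds 0.5 or 1.0 per SD).

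| Intervention dropout | Log-odds per SD | Raw month-6 difference (t-test rejection) | Adjusted for outcome's own baseline (rejection) | Using week-12 data |
|---|---|---|---|---|
| 16% | 0.5 | 0.046 (9.5%) | 0.019 (5.6%) | 0.000 |
| 26% | 0.5 | 0.079 (17.4%) | 0.032 (8.4%) | 0.002 |
| 19% | 1.0 | 0.098 (25.2%) | 0.040 (10.6%) | −0.001 |
| 29% | 1.0 | 0.149 (47.7%) | 0.063 (17.5%) | 0.003 |

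The true value is 0, so each entry is bias in SD units. Repeat runs put the baseline-adjusted range at 0.02–0.07.

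**Why the columns differ.** Let d be the shift in the mean week-12 score among intervention children who remain, and ρ the common correlation. Baseline and month 6 each shift by ρd. Then:
- raw month-6 bias = ρd;
- bias adjusted for the outcome's own baseline ≈ ρd − ρ·ρd = ρd(1 − ρ);
- bias of the change from baseline = ρd − ρd = 0.

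With ρ = 0.6, the second line is 0.4 times the raw bias: 0.4 × 0.046 = 0.018, 0.4 × 0.079 = 0.032, 0.4 × 0.098 = 0.039, 0.4 × 0.149 = 0.060. These agree with the simulated 0.019, 0.032, 0.040 and 0.063. Simulated change scores in the same design (intervention dropout 17–29%) had bias of −0.002 to 0.003 SD and rejection of 5.0–5.8%. The zero depends on week 12 correlating equally with baseline and with month 6.

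**Second simulation**, to vary the mechanism: 600 replicates; true effects 0.3 SD at week 12 and 0.2 SD at month 6; correlation 0.5 or 0.7; month-6 dropout about 10–30%; log-odds 0.7 per SD where dropout depends on week 12.
- Dropout random: bias at most 0.01 SD.
- Dropout dependent on week 12 equally in both groups: at most 0.01 SD.
- Dropout dependent on week 12 in the intervention group only: 0.04–0.14 SD raw and 0.02–0.05 SD adjusted for own baseline.
- Estimate using all visits: at most 0.01 SD in every case.

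**Sample size of the t-test.** Section 2.4 uses unpaired tests within sex only. At an assumed half sample (144 v 279), the bias is unchanged, but worst-case rejection falls from about 48% to about 26–27%.

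**The case against.** The case against is substantial.

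- **No analysis set is stated.** A reader might infer that only attenders are analysed. The article does not say so. It states no missing-data rule, and an article commonly leaves that to the full documents. This stands: the point rests on what the named methods can use, not on that silence.
- **Voluntary refers to app and device use.** A reader might infer that poorly engaged children leave the study in Phase 3. Section 2.2.3 makes only continued use voluntary and plans the month-6 assessment in both groups. Section 2.2 describes PAPS reporting as compulsory for schools. Stopping the app is not missing the assessment, so differential loss is a possibility and not a documented feature.
- **Outcomes are worded as changes.** Section 2.3 speaks of behavioural changes and changes in anthropometry. If change scores are analysed, the bias can vanish, as shown above. Section 2.4 does not settle whether raw values or changes are compared, so this limits the size of the problem without removing it.
- **A month-6 regression does estimate a long-term effect.** This is right. A reader might say that persistence is never estimated, but that goes too far. What is missing is a specified between-group contrast of the two effects.
- **Per-visit regression is legitimate.** True with little or non-differential dropout. It still discards information already collected, and the alternative costs little.

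**Conclusion.** The point holds as a vulnerability, not as a demonstrated bias. Section 2.4 names only methods for one or two visits in a three-visit design, omits the outcome's own baseline from the combined-sex regression for the primary outcomes, and specifies no contrast between the week-12 and month-6 group effects.

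The size rests entirely on assumed dropout. It is about 0.05–0.15 SD for raw month-6 scores, and 0.02–0.07 SD with own-baseline adjustment, if intervention dropout is 16–29% and depends on the week-12 score while control dropout is random. It is about 0 if dropout is random or equally outcome-related in both groups, or if change scores are used with equal correlations. The article does not support saying that the month-6 result is biased. It supports saying that the named methods give no protection if loss turns out to be differential. The change is worth making because it is cheap and the week-12 data are already planned.

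**What to change.** For each outcome measured in both groups, replace the separate per-visit group comparisons in section 2.4 with one repeated-measures model over all enrolled children with any follow-up:

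- a linear mixed model for continuous outcomes, with unstructured within-child covariance, or a logistic mixed model for binary outcomes;
- terms for group, visit (week 12, month 6), group-by-visit, the outcome's baseline value and sex;
- three reported results: the group difference at week 12, the group difference at month 6, and the difference between them, the last being the test of persistence.

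**Cost.** Section 2.4 is rewritten. Data collection does not change, and SPSS can fit the models.

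**Limits.** The model relies on missing-at-random, so dropout that depends on unobserved month-6 values would still bias it. It does not solve the single control school, clustering by school, or the use of school and app usage as covariates. Those need separate attention.
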